### Trials Protocols

#### SAAF-T

##### A. SPECIFIC AIMS

In this proposal, we request funding to conduct a randomized prevention trial to test the SAAF–HS program’s efficacy. The sample will include ~500 rural African American families with a 10th-grade student, half of whom will be assigned randomly to a SAAF–HS and half to an attention-control group. Pre-intervention, post-intervention, and long-term follow-up assessments of adolescents’ substance use and high-risk sexual behavior will be gathered from the entire sample.

Our specific aims are as follows:

1. To test the hypothesis that rural African American adolescents randomly assigned to participate in SAAF–HS, compared to attention-control participants, will demonstrate lower rates of substance use initiation, and that those who already use substances (e.g., cigarettes; alcohol, including binge drinking; marijuana and other illicit substances) will use them less frequently and consume lower quantities at each follow-up assessment.
2. To test the hypothesis that rural African American adolescents randomly assigned to participate in SAAF–HS, compared to attention-control participants, will demonstrate lower rates of high-risk sexual behavior (e.g., instances of unprotected sexual intercourse, multiple sexual partners) at each follow-up assessment.

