##### D. RESEARCH METHODS

###### D.1. Participants

A random sample of 500 rural African American families with a son or daughter in the first semester of 10th grade in a public high school will participate in the study.

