### **D.8.6. Statistical Power**

In this section, we discuss statistical power for the models we described previously, including the SAAF–HS intervention’s impact on changes in the slopes of drug use and high-risk sexual behavior and on outcomes at a single point in time. In these calculations, we assume conservatively a 13% loss in data across time, yielding two groups of 250 participants in each condition. For growth models with either continuous or discrete outcomes, we have used power calculations that Brown and colleagues have made available on the internet (<http://psmq.usf.edu/products.html>) to determine the smallest effect size we can detect with 80% power for changes in the slope parameter, assuming linear growth over three time points. When the measurement reliability is 60%, we can achieve 80% power when the ES is 0.1 at posttest and grows to 0.2 at long-term follow-up. For conducting a test at a single time point on a continuous outcome, based on Cohen (1988), we can detect an effect size of 0.25 at 80% for a 0.05 level test, assuming negligible variation based on school. We also have calculated power by taking this factor into account. Based on variability observed in other preventive trials among schools and individuals (Brown and Liao, 1999) the power is 80% to detect an ES of 0.36 and 70% to detect an ES of 0.31 for 0.05 level tests. Thus, we clearly have adequate power to detect a moderate effect for continuous outcomes involving single time points. For a discrete measure at a single time point, such as a comparison of the proportion of individuals who are using a substance, we will be able to detect an odds ratio of at least 1.6 with 80% power using a 0.05 level chi-square test (Fleiss et al., 2003). This odds ratio corresponds to a reduction from 50% users to 38% in the intervention group.

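### SAAF-T power section: 500 enrolled less 13% leaves about 217 per arm, not 250, and the odds ratio of 1.6 falls short of 80% power at either number

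*Combined protocol and SAP*

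**What the plan says.** All references are to the SAAF-T part of the combined document.

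- **Enrolment.** Section A (Specific Aims): "The sample will include ~500 rural African American families with a 10th-grade student", "half of whom will be assigned randomly" to the programme and the rest to attention control. Section D.1 gives the same number without the approximation sign: "A random sample of 500 rural African American families with a son or daughter in the first semester of 10th grade".
- **Number used for power.** Section D.8.6: "we assume conservatively a 13% loss in data across time, yielding two groups of 250 participants in each condition". The sentence introduces the calculations of that section as a whole.
- **Continuous outcome, one time point.** "we can detect an effect size of 0.25 at 80% for a 0.05 level test, assuming negligible variation based on school". With school variation allowed for, "the power is 80% to detect an ES of 0.36 and 70% to detect an ES of 0.31 for 0.05 level tests". No intraclass correlation or variance component is given.
- **Binary outcome, one time point.** "we will be able to detect an odds ratio of at least 1.6 with 80% power using a 0.05 level chi-square test". The section equates this with a fall from 50% to 38% users. It states no allowance for school here.
- **Growth model.** 80% power for an effect of 0.1 at posttest rising to 0.2 at long-term follow-up, with 60% reliability. No other inputs are given.

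**The concern.** The 250 per arm described as what remains after attrition is exactly half of the enrolled 500. The loss allowance is named, and called conservative, but does not appear to have been taken off. A reader of D.8.6 would believe that 80% power survives a 13% loss.

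The binary figure raises a second question that does not depend on attrition: whether 250 per arm gives 80% power for the stated odds ratio at all. Initiation and use versus non-use are Aim 1 outcomes, so this is the figure a reader would use to judge what a null result on them means.

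**Working it through.** **Inputs.** 500 families, 1:1 allocation (A, D.1); 13% loss, 250 per arm, 0.05 level, effect 0.25, odds ratio 1.6, 50% versus 38% (D.8.6). The plan does not state sidedness. An effect of 0.25 at 80% power needs 252 per arm two-sided but only 198 one-sided, so the continuous figure is two-sided, and I use two-sided tests throughout.

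**1. Number per arm.** 500 × 0.87 = 435, and 435 / 2 = 217.5. In reverse, 500 / 0.87 = 574.7, so about 575 must be enrolled to keep 250 per arm.

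**2. Continuous outcome, no school effect.** Power = Φ(d√(n/2) − 1.96); detectable d = (1.96 + 0.8416)√(2/n).

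- n = 250: 0.25 × √125 = 2.795; Φ(0.835) = 0.798. Detectable d = 2.8016 × 0.08944 = 0.251. This reproduces the plan's figure, so it was computed with 250.
- n = 217: 0.25 × √108.5 = 2.604; Φ(0.644) = 0.740. Detectable d = 2.8016 × 0.09600 = 0.269.

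**3. Binary outcome.** Power = Φ{(|p1 − p2|√n − 1.96√(2p̄q̄)) / √(p1q1 + p2q2)}, without continuity correction.

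For 50% versus 38% (odds ratio 1.63), p̄ = 0.44, 1.96√(2p̄q̄) = 1.376 and the denominator is 0.697.

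- n = 250: (0.12 × 15.811 − 1.376) / 0.697 = 0.748; power 0.773.
- n = 217: (0.12 × 14.731 − 1.376) / 0.697 = 0.562; power 0.713.

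An odds ratio of exactly 1.6 from 50% gives p2 = 1/2.6 = 0.3846. The same formula gives 0.740 at 250 and 0.678 at 217.

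| Per arm | Power, d = 0.25 | Detectable d | Power, 50% vs 38% | Power, OR 1.6 | Detectable OR from 50% |
|---|---|---|---|---|---|
| 250 | 0.798 | 0.251 | 0.773 | 0.740 | 1.66 (p2 = 0.376) |
| 217 | 0.740 | 0.269 | 0.713 | 0.678 | 1.72 (p2 = 0.367) |

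For 80% power, 50% versus 38% needs 268 per arm (284 with continuity correction), and an odds ratio of 1.6 needs 290 (307). The plan's binary figure is nearly reproduced only by a one-sided, continuity-corrected calculation for an odds ratio of 1.6, which needs 246 per arm.

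**4. School-adjusted and growth figures.** The inputs are not in the documents, so these cannot be recomputed. If they used 250 per arm and all variance scales with 1/n, the detectable effects grow by √(250/217) = 1.073. Then 0.36 becomes 0.386, 0.20 becomes 0.215, and a stated 80% becomes about 74%. The growth is smaller if part of the variance does not depend on the number of families.

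**The case against.** **The error may be in the enrolment figure.** Taken literally, D.8.6 gives 250 as the number after loss. If that was intended, the enrolment target should read about 575 and the 0.25 figure stands. The documents do not settle this, so the remedy must begin with reconciliation. The binary shortfall remains on either reading.

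**The planned analysis is more efficient than the test checked here.** D.8.2 adjusts single-time-point analyses for baseline. If the baseline–outcome correlation were 0.2, 0.36 or 0.5 (assumed values; the plan gives none), power for 0.25 at 217 per arm would be about 76%, 80% or 85%. D.8.1 also uses all available data under full maximum likelihood, so 217 complete cases is a floor for the growth models. Both points stand and limit the practical loss for continuous outcomes. Neither makes the stated calculation correct, because D.8.6 takes no credit for baseline adjustment and defines its number as after loss.

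**Stronger readings that the documents do not support.**

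- A reader might infer that every figure in D.8.6 is shown to be wrong. The school-adjusted and growth figures lack the inputs to test that. A growth model with a within-person correlation of 0.6 and a common pretest mean does give 0.805 at 250 per arm. But correlations of 0.5 and 0.7 give 0.75 and 0.88, and dropping the common mean gives 0.71, so the match is not evidence.
- A reader might carry the school inflation implied for continuous outcomes over to the binary one. The plan's own pairs imply different values, (0.36/0.25)² = 2.07 at 80% power and about 1.95 at 70%, and nothing shows that either applies to a proportion.
- It would be wrong to say that detectable effects are overstated. Power is overstated; the detectable effects are understated.

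**The prevalence condition is disclosed.** D.8.6 does tie its odds ratio to 50% versus 38%. What it lacks is a statement that the figure does not hold at other prevalences.

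**Conclusion.** The point holds in two parts. First, 500 enrolled, a 13% loss and 250 per arm remaining cannot all be true. With 500 enrolled, about 217 per arm remain, power for an effect of 0.25 falls about 6 points to 74%, and the detectable effect is about 0.27. Second, and independently of attrition, the odds-ratio claim misses 80% two-sided at 250 per arm (77% and 74%) and misses by more at 217 (71% and 68%), where the detectable odds ratio is about 1.72.

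These figures assume a two-sided 0.05 test, complete cases, no baseline adjustment, no school effect and, for the odds ratio, 50% prevalence in the control arm. The size is modest for continuous outcomes and larger for the binary ones. No conclusion is drawn about the school-adjusted and growth figures beyond the need to rerun them.

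**What to change.** 1. Reconcile sections A and D.1 with D.8.6: say whether 250 per arm is the number enrolled or the number expected after loss.
2. If enrolment stays at 500, restate D.8.6 on about 217 per arm: detectable effect 0.27 for a continuous outcome without school variation, and odds ratio 1.72 (50% to about 36.7%) for a binary one. If 250 per arm after loss was meant, correct enrolment to about 575, keep 0.25, and change the odds ratio to 1.66.
3. State sidedness, and say that the odds ratio holds only at 50% prevalence and without school variation.
4. Rerun the school-adjusted and growth calculations at the corrected number with the inputs the investigators used, and report those inputs. As a guide, if all variance scales with 1/n, 0.36 becomes at most about 0.39 and 0.20 about 0.215. These are bounds for checking, not replacement text.

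With enrolment kept at 500 the cost is wording, one rerun and slightly less favourable stated figures. Raising enrolment would mean about 75 more families.

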###### ***D.1.1. Eligibility, Random Assignment, and Contamination***

Lists of all African American 10th-grade students will be obtained from each of the 6 participating high schools. The students on each school’s list will be randomly ordered to determine the sequence in which families will be contacted to be screened for eligibility. A small number of students will be excluded from the pool of potential participants. If the primary caregiver or adolescent does not speak English, which is unlikely, the youth will be excluded. Twins and stepsiblings who both are in the 10th grade will be excluded because the inclusion of more than one participant from the same family introduces confounds that make interpretation difficult. Youth from families who have taken part in any of the investigators’ other studies will also be excluded. Although this is unlikely because participants for the proposed study will not be recruited from counties that were sampled for previous research, some participants may have moved to one of the targeted counties.

Enrolled families will be assigned randomly to either the SAAF–HS or attention-control condition (see recruitment procedures, section D.1.2). All families will be followed across the course of the proposed study and assessed regardless of the number of SAAF–HS or attention-control sessions they do or do not attend (an intent-to-treat analysis); this includes youth who drop out of school during the study.

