### **D.8.2. Analyses for Aims 1 and 2: Primary Outcomes**

The primary issue to be addressed in Aims 1 and 2 is SAAF-HS's effectiveness in deterring the onset and escalation of substance use and high-risk sexual behavior across the 18 months separating the pretest and long-term follow-up assessments. A dramatic growth in substance use and high-risk sexual behavior is likely to occur across measurement points, which include the beginning of 10th grade, middle of 10th grade, and beginning of 11th grade. SAAF-HS's impact on each of the outcomes will be examined in three ways: on posttest (middle of 10th grade), on long-term follow-up (beginning of 11th grade), and on growth trajectories. The two single-time-point analyses will be conducted with Structural Equation Modeling (SEM) using the maximum likelihood method and controlling for baseline levels of substance use and high risk-sexual behavior. The first outcome analysis (posttest) identifies reduction in substance use and high risk-sexual behavior; the second (long-term follow-up) will be used for tests of delayed initiation and reduction of substance use and reduction of high-risk sexual behavior. We will explore, in an additional analysis, SAAF-HS's effects on delaying the onset of sexual intercourse. SAAF-HS, however, is likely to have its strongest impact on growth trajectories (Taylor et al., 2000). A baseline growth model with random intercepts and slopes will be established for the attention-control condition. A multigroup analysis will then be conducted, testing the equivalence of growth parameters between the attention-control and the SAAF-HS groups (Byrne, 2001). If the multigroup analyses detect differences between the slopes (rates of growth for substance use or high-risk sexual behavior) of the SAAF-HS and attention-control group, impact statements will be made by examining how the average substance use and sexual risk behavior trajectories change with time.

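### SAAF-T D.8.6: the school-adjusted power figures (80% at ES 0.36, 70% at ES 0.31) match no analysis in the plan, and the D.8.2 models contain no school term

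*Combined protocol and SAP*

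**What the plan says.** **Design.** SAAF-T D.1.1 recruits through schools: "Lists of all African American 10th-grade students will be obtained from each of the 6 participating high schools". It randomises below that level: "Enrolled families will be assigned randomly to either the SAAF–HS or attention-control condition". The text does not say whether randomisation is stratified by school.

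**Analysis.** In D.8.2, "The two single-time-point analyses will be conducted with Structural Equation Modeling (SEM) using the maximum likelihood method and controlling for baseline levels" of the outcomes. Growth is tested with random intercepts and slopes compared between conditions in a multigroup model. D.8.1 and D.8.2 add two-part, binary, Poisson and zero-inflated models. None of them has a school fixed effect, a school random effect, a cluster-robust variance or a school-by-condition term.

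**Power.** D.8.6 says that it covers the models described before it. It first states that "we can detect an effect size of 0.25 at 80% for a 0.05 level test, assuming negligible variation based on school". It continues: "We also have calculated power by taking this factor into account", and gives 80% power at ES 0.36 and 70% at ES 0.31, taking the variability from a cited source without stating its value. The sentence with these figures opens: "Based on variability observed in other preventive trials among schools and individuals (Brown and Liao, 1999) the power is 80% to detect an ES of". On sample size, "we assume conservatively a 13% loss in data across time, yielding two groups of 250 participants in each condition", although D.1 plans "A random sample of 500 rural African American families" in total.

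The AIM plan in the same file does address school: its D6.1d brings school-level effects into the hypothesis tests if they explain unique variance at baseline. SAAF-T has no such rule.

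**The concern.** A power statement should describe the test that will be run. Here the less favourable pair of figures allows for school, but the tests do not. When families are randomised within schools, a school with high or low substance use contributes to both arms, so differences in level between schools largely cancel from the arm contrast. A rise in the detectable ES from 0.25 to 0.36 therefore needs something more, such as randomisation of whole schools or a programme effect that differs between schools. The plan names neither.

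Two things are at stake. A reader cannot tell which detectable effect belongs to the single-time-point tests of Aims 1 and 2. And a design variable that the trial already holds, and that D.8.6 treats as important enough to count, is left out of the models.

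**Working it through.** **Inputs.** From D.8.6: 250 per arm, 0.05 level, ES 0.25 at 80% without school, ES 0.36 at 80% and 0.31 at 70% with school, 13% loss. From D.1 and D.1.1: 500 families, 6 schools, about 500/6 = 83.3 families per school. From D.3.1: delivery groups of 10 to 12 families in both arms. Assumed: SD 1, 1:1 allocation, two-sided test, no baseline adjustment.

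**1. The plan's figure without school.** SE = √(2/250) = 0.0894. Detectable ES at 80% = (1.960 + 0.842) × 0.0894 = 0.251. This reproduces 0.25. A one-sided test would give 87.5% power at 0.25, so a two-sided test was evidently used.

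**2. That same test at the school-adjusted effect sizes.** Power = Φ(ES/SE − 1.960).

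| Analysed per arm | ES 0.25 | ES 0.31 | ES 0.36 |
|---|---|---|---|
| 250 | 79.8% | 93.4% | 98.1% |
| 217 | 74.0% | 89.8% | 96.3% |

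The stated 70% at 0.31 and 80% at 0.36 are not the power of this test at either sample size.

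**3. What 0.36 could mean.** Under a normal test the implied SE is 0.36/2.802 = 0.1285, a variance inflation of (0.1285/0.0894)² = 2.06. From 0.31 at 70% the SE is 0.31/2.484 = 0.1248 and the inflation 1.95. Very different structures can yield 0.36 at 80%:

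| Structure assumed | Value needed |
|---|---|
| Whole schools randomised, normal test | ICC = (2.06 − 1)/(83.3 − 1) = 0.013 |
| Whole schools randomised, t on 4 df | inflation 1.15, ICC about 0.0018 |
| Families randomised, effect varies by school, normal test | variance of effect = 6 × (0.1285² − 0.008) ≈ 0.05 SD² |
| Families randomised, effect varies by school, t on 5 df | SE 0.1025, variance ≈ 6 × (0.1025² − 0.008) = 0.015 SD² |

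The documents do not allow a choice among these. The two stated figures agree only roughly with each other: with the SE implied by 0.36, power at 0.31 is 67.5% (normal) to 68.2% (4 df). Rounding of both effect sizes could just close the gap, so nothing is built on it.

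**4. School as a fixed factor, families randomised.** Detectable ES = 0.251 × √(1 − ICC). The ICC is assumed, because the plan gives none.

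| School ICC | 250 per arm | 217.5 per arm |
|---|---|---|
| 0 | 0.251 | 0.269 |
| 0.05 | 0.244 | 0.262 |
| 0.10 | 0.238 | 0.255 |

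School-level variation lowers the detectable ES slightly once school is in the model; it does not raise it to 0.36.

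**5. Sample size after loss.** 500 × 0.87 = 435, or 217.5 per arm. The 250 per arm in D.8.6 is the full enrolment, with no loss taken off; 250 per arm after a 13% loss would need 500/0.87 ≈ 575 families.

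**6. Delivery groups.** For groups of 11, the design effect is 1 + 10 × ICC. At assumed group ICCs of 0.05 and 0.10 it is 1.5 and 2.0, and the detectable ES at 250 per arm is 0.251 × √1.5 = 0.31 and 0.251 × √2.0 = 0.35.

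**The case against.** The best defence is that D.8.6 openly shows two cases, one with negligible school variation and one with an allowance for it, and that a cautious sizing case need not be the primary model. That is reasonable, and 0.36 and 0.31 could serve in that role. But D.8.6 does not label them so, and the case cannot be assessed without its variance and degrees of freedom. The claim of adequate power for a moderate effect also does not hang on 0.36 in particular; it reads the same at 0.25.

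The available text passes from D.8.3 to D.8.6, so a school term in an intervening section cannot be excluded. The finding is limited to what is there.

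Three stronger readings are tempting, and the documents do not support them.

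- **That 0.36 and 0.31 are arithmetic errors, or the penalty for randomising whole schools.** The inflation of 2.06 is back-solved from one reading; on 4 df it is 1.15. The figures are uncheckable, not refuted.
- **That the D.8.2 tests have a false-positive rate of about 17%.** That value is 2 × [1 − Φ(1.960 × 0.0894/0.1285)]. It holds only on a normal-theory reading of 0.36, for inference beyond these six schools, and with effects that differ by school yet average zero. It disappears if the target is the average effect over the six schools.
- **That 0.25 is the true detectable effect once 0.36 is removed.** This would ignore both the 13% loss and the delivery groups. Deleting the only figures that allow for any clustering, with no caveat, would leave the plan too optimistic.

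**Conclusion.** The point stands as a mismatch between the power section and the analysis section. The school-adjusted figures belong to no SAAF-T model in the available text, and the plan does not say how school is handled. For the simple two-sample comparison behind the 0.25, power at 0.36 and 0.31 is about 98% and 93% at 250 per arm, or about 96% and 90% at 217. These values assume a two-sided 0.05 test, no baseline adjustment and no group clustering. They are therefore not the exact power of the baseline-adjusted SEM, which could gain from the baseline covariates and lose from clustering in delivery groups. The conclusion that school level alone would not move 0.25 to 0.36 rests on family-level randomisation with both arms present in each school. Neither a miscalculation nor an inflated false-positive rate is established.

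**What to change.** 1. **D.8.2.** Add school of recruitment as a fixed factor (five indicators) to the Aim 1 and Aim 2 SEM and growth models. Define the effect as the average over these six schools, and report school-by-arm as a sensitivity analysis. In the multigroup growth model, hold the school coefficients equal across arms in the main analysis.
2. **D.8.6.** Give power for that test: an 80%-power ES of about 0.25 if 250 per arm are analysed, or about 0.27 at about 217 per arm (500 families less 13%), before any gain from baseline adjustment. State which sample size applies.
3. **D.8.6.** Keep 0.36 and 0.31 only if they are labelled as a conservative sensitivity scenario, with the structure (for example, programme effects that vary by school), the assumed variance and the degrees of freedom stated. Otherwise remove them.
4. **D.8.6.** Say that the restated figures exclude clustering by delivery group, and show the range: about 0.31 to 0.35 at 250 per arm for assumed group ICCs of 0.05 to 0.10.

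The cost is wording in two sections, five degrees of freedom in each equation that school enters, and slightly more complex models. School is already known from the recruitment lists, and the conduct of the trial does not change.

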#### **D.7.7. Adolescents' Outcomes**

**D.7.7a. Substance use.** The substance use assessment is designed to address its multidimensional nature (Newcomb, 1992). From three well-validated measures, items were selected for their sensitivity to intervention effects at several levels of substance use. At the initiation level, group differences in the proportion of participants who transition from nonuse to use during the study can be detected. At the escalation level, group differences in the proportion of participants who increase their frequency/intensity of use during the study can be assessed. At the problem use level, group differences in specific substance-related behaviors and problems can be determined. The basic items in the measure are those included in the Monitoring the Future study (Johnston et al., 2004) that assess lifetime, annual, and 30-day prevalence and frequency of cigarette smoking, alcohol use, binge drinking, and marijuana use. For the purposes of the proposed study, a 6-month assessment at the long-term follow-up will be added. A checklist of other drugs includes lifetime use of LSD/acid, MDMA/Ecstasy, cocaine, heroin, other opiates, amphetamines, non-prescribed tranquilizers, and inhalants. Problems associated with substance use will be indexed using items from the Minnesota Student Survey for high school students (Harrison, Fulkerson, & Beebe, 1998) These scales include items assessing dependence (e.g., had to use more to get same effect, tried to cut down but couldn't) and negative consequences of use (e.g., use hurt relationships with friends or family, use interfered with other activities, use resulted in problems with law, missed school or work because of use).

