The three-time-point design allows one degree of freedom in fitting linear growth patterns. An exploratory analysis will be conducted to assess nonlinearity in growth over time (Wang, Brown & Bandeen-Roche, 2005). If these diagnostic patterns indicate nonlinearity, the fit will be improved through transformation of the time axis by freeing the last loading, effectively incorporating nonlinearity. Separate analyses will be used to examine impact on alcohol, tobacco, and marijuana use because different intervention impacts occasionally emerge for different substances. In all these models, fit will be compared using formal likelihood ratio statistics, Wald-type tests, and diagnostic techniques that Brown and colleagues developed (Wang, Brown & Bandeen-Roche,

2005). For analyses of high-risk sexual behavior, two outcomes, unprotected sex at last encounter and number of unprotected encounters in the past 3 months, will be analyzed using binary outcomes and Poisson counts, respectively. For each of these repeated measures, we anticipate two types of “zeros”: one indicating abstinence and another indicating condom use. Two approaches will be used, one that incorporates a separate model of abstinence and condom use over time as a function of intervention condition and another that models these outcomes as “zero-inflated” Binomial and Poisson models, similar to Carlin et al.’s (2002) modeling of smoking behavior.

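### SAAF-T D.8.6: 250 per arm gives 74% to 77% power for the stated odds ratio, not 80%, and the figure does not carry over to less common substances or to initiation

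*Combined protocol and SAP*

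**What the plan says.** SAAF-T section D.8.6 (Statistical Power) works from a stated sample after attrition, "yielding two groups of 250 participants in each condition". For a discrete outcome at a single time point, "such as a comparison of the proportion of individuals who are using a substance", it says "we will be able to detect an odds ratio of at least 1.6 with 80% power using a 0.05 level chi-square test". It illustrates the effect: "This odds ratio corresponds to a reduction from 50% users to 38% in the intervention group".

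Three other places in SAAF-T bear on how far that figure reaches:

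- Aim 1 in section A opens with lower rates of initiation. Section D.7.7a describes the initiation level of measurement as one where "group differences in the proportion of participants who transition from nonuse to use during the study can be detected". Section D.8.2 plans a test of delayed initiation at long-term follow-up.
- Section D.8.2 also says "Separate analyses will be used to examine impact on alcohol, tobacco, and marijuana use".
- Section D.8.1 expects many abstainers in the substance use variables but gives no percentage.

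No SAAF-T section gives a prevalence for a named substance, the share of nonusers at pretest, or an initiation rate.

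**The concern.** The statement reads as a general guarantee for binary substance use outcomes. Two things looked doubtful. First, 250 per arm seemed slightly too few for 80% power at the stated rates. Second, the calculation rests on one control rate, 50%, and on every participant contributing. Neither need hold when each substance is tested separately, and the second cannot hold for initiation if any participant already uses the substance at pretest.

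The stake is interpretation. A reader who takes 1.6 as detectable for every binary comparison could treat a null result for a less common substance, or for initiation, as stronger evidence against the programme than the design supports.

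**Working it through.** **Inputs.** From D.8.6: n = 250 per arm, 0.05 level chi-square test, 80% power, odds ratio 1.6, rates 50% and 38%. Sidedness is not stated. Two-sided is used because a chi-square test is two-sided by nature, and because the same section's continuous figure (effect size 0.25) reproduces two-sided: Φ(0.25 × √125 − 1.96) = 79.8%. No school effect is included.

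D.8.6 also says "we assume conservatively a 13% loss in data across time", while section D.1 enrols 500 families. 500 × 0.87 = 435, or about 217 per arm, so 250 is not the number left after that loss. That is a separate matter; everything below keeps the plan's 250.

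**Formula.** Power = Φ{ [ |p1 − p2| − 1.96 × √(2p̄(1 − p̄)/n) ] / √([p1(1 − p1) + p2(1 − p2)]/n) }, where p̄ = (p1 + p2)/2.

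**Step 1: the plan's own case.**

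- 50% versus 38%: the odds ratio is 1/(0.38/0.62) = 1.63. The null standard error is √(2 × 0.44 × 0.56/250) = 0.0444 and the alternative one is 0.0441. (0.12 − 1.96 × 0.0444)/0.0441 = 0.748, so power is **77.3%**. For 80%, 268 per arm are needed.
- Exactly 1.6 from 50%: odds 1/1.6 = 0.625, so p2 = 0.625/1.625 = 38.5%. (0.1154 − 1.96 × 0.0444)/0.0441 = 0.642, so power is **74.0%**. For 80%, 290 per arm are needed.
- Other methods agree: arcsine 77.3% and 74.0%; Wald test on the log odds ratio 76.9% and 73.6%; with continuity correction 74.5% and 70.9%.
- Solving for 80% power at a 50% control rate gives p2 = 37.6%, an odds ratio of **1.66**. The stated figure looks like a rounding of this (37.6% to 38%, and 1.66 cut to 1.6).
- Over all control rates, power for 1.6 at 250 per arm peaks at **74.5%**, at a control rate of about 56%.

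**Step 2: other control rates, all 250 per arm contributing.** The control rates are assumed. The last column is the intervention rate at the detectable odds ratio.

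| Control rate | Power for OR 1.6 | OR detectable at 80% | Intervention rate |
|---|---|---|---|
| 50% | 74% | 1.66 | 37.6% |
| 40% | 70% | 1.70 | 28.2% |
| 30% | 62% | 1.80 | 19.2% |
| 20% | 49% | 2.03 | 11.0% |
| 10% | 30% | 2.90 | 3.7% |

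**Step 3: initiation.** Only pretest nonusers of a substance can start using it. Aim 1 refers to participants who already use, and eligibility (D.1.1) sets no condition on use, so the initiation set is smaller than 250 per arm. Step 1 shows that 1.6 misses 80% even at 250, so it misses at any smaller number. Examples with assumed values: 225 nonusers per arm and 20% of controls initiating give 45% power (detectable odds ratio 2.13); 175 and 20% give 37% (2.40).

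That holds the odds ratio at 1.6. Suppose instead that the whole 50%-to-38% difference arises through initiation, with pretest users counted as users at follow-up in both arms. The rates among nonusers are then (0.50 − u)/(1 − u) and (0.38 − u)/(1 − u), where u is the pretest user share:

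| Pretest users (u) | Nonusers per arm | Rates among nonusers | OR | Power |
|---|---|---|---|---|
| 10% | 225 | 44.4% vs 31.1% | 1.77 | 83% |
| 20% | 200 | 37.5% vs 22.5% | 2.07 | 91% |
| 30% | 175 | 28.6% vs 11.4% | 3.10 | 98% |

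Initiation power therefore ranges from poor to ample, depending on inputs that the plan does not state.

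**The case against.** The strongest reply is that the plan never claims 1.6 for initiation. Its example is current use, and its explicit assurance of adequate power is limited to continuous outcomes. This stands: for initiation the problem is a missing figure, not a false one.

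A reader might infer that the initiation hypothesis is underpowered. The documents do not support that. As the last table shows, the plan's illustrated difference, if it comes wholly through initiation, implies a larger odds ratio among nonusers and power above 80%. That scenario is an assumption too, but so is a fixed 1.6.

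A reader might also infer that the planning population cannot fit the initiation population: either half already use at pretest, or the 50% rate is wrong. That confuses two times. The 50% is the control rate at an outcome assessment, and D.8.2 expects use to grow markedly between assessments. Low pretest use and 50% use at follow-up are compatible.

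Nor is this the only planning figure for discrete outcomes. D.8.6 also gives 80% power for growth models with continuous or discrete outcomes (effect size 0.1 at posttest growing to 0.2), and D.8.2 expects the strongest impact on trajectories. The planned structural equation models adjust for baseline and may be more powerful than a chi-square test. But D.8.6 makes this claim for a chi-square test, and it gives no initiation power for those models.

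One variant does reproduce the figure: one-sided, continuity-corrected, exactly 1.6, giving 80.7%. It does not fit a chi-square test or the section's own two-sided continuous figure.

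Finally, for a substance used by 40% to 60% of controls, the detectable odds ratio is 1.66 to 1.70, close to the plan's own case. The material loss comes below about 40%.

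**Conclusion.** The statement is wrong as written, by a small margin at its own inputs: 77% power for 50% versus 38%, 74% for an odds ratio of exactly 1.6, and a detectable odds ratio of 1.66. This part rests only on the plan's figures and a two-sided 0.05 test.

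The figure should not be applied to substances with use well below 50%. At control rates of 30%, 20% and 10%, power for 1.6 is 62%, 49% and 30%. These rates are assumed; the expectation of many abstainers makes lower rates plausible but does not quantify them.

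For initiation, a fixed odds ratio of 1.6 cannot reach 80% power with fewer than 250 nonusers per arm under this test. Whether the hypothesis itself is adequately powered is not established either way.

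**What to change.** In SAAF-T D.8.6:

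1. Restate the single-time-point binary figure as a detectable odds ratio of about 1.66 at a 50% control rate, with 250 per arm and a two-sided 0.05 test.
2. Tabulate the detectable odds ratio, with the matching risk difference, for control rates from 50% to 10%, and say which substances are expected to fall where.
3. Add a separate initiation calculation for each substance, based on the expected number of pretest nonusers and their expected initiation rate. State the effect both as an odds ratio and as a risk difference, because a given difference in overall use implies a larger odds ratio among nonusers.

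If the number per arm is revised for attrition, these figures should be recomputed on the revised number. The cost is a few sentences and a table, plus the sponsor's prevalence and initiation assumptions; no extra enrolment. The stated detectable effect becomes less favourable.
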